#### Phototherapy

Phototherapy will be administered with a portable nine-diode cluster (PainAway™, Multi Radiance Medical, Solon, Ohio, United States), with one 905-nm diode (mean power: 1 mW; peak power: 10 W; spot size: 0.44 cm^2^), four 875-nm diodes (mean power of each diode: 17.5 mW; spot size: 1 cm^2^) and four 670-nm diodes (mean power of each diode: 15 mW; spot size: 1 cm^2^); frequency: 1000 Hz; 300-second irradiation time in each quadrant; total energy: 39.3 J per quadrant. The portable nine-diode cluster will be used overlapping three quadrants of the knee in random sequence: medial quadrant, lateral quadrant, and posterior quadrant. These quadrants were chosen to overlap the reference points employed in a study using a LLLT device with a smaller irradiation area [10].

#### Exercise program

The program will include three weekly 45 to 60-minute sessions over the course of eight weeks (24 sessions) and will be organized in three phases: 1) weeks one to two, improvements in balance and coordination, each exercise will have 30 repetitions and two sets; 2) weeks three to five, each exercise will have 20 repetitions and three sets; and 3) weeks six to eight, each exercise will have 20 repetitions and three sets [28].

Phase 1: 10 minutes of warm up on a treadmill; participant seated with weight on ankle extends the knee and performs internal and external rotation on each leg; in the supine position on a cot, from maximum knee flexion, the participant slowly performs maximum knee extension on each leg; in the standing position, the participant flexes the knee to 60° and performs knee extension; the participant walks along a three-meter line; if the participant steps outside the line, he/she must return to the initial position and in the standing position, the participant transfers weight from one leg to the other.

Phase 2: In the standing position, the participant flexes the knee to 60° and performs knee extension; the participant walks sideways crossing the legs to the right and to the left; in the standing position, the participant maintains his/her balance on a balance board; In the supine position on a cot, the participant performs maximum knee flexion on each leg;in the standing position, the participant positioned on a step flexes one knee and squats, followed by extension; the same is performed with the other leg.

Phase 3: The participant walks sideways crossing the legs to the right and to the left; in the standing position, the participant flexes the knee to 60° on each leg; in the standing position, the participant maintains his/her balance on a balance board; the participant is then asked to close his/her eyes; in the standing position, the participant holds the toes flexed for 1 to 2 seconds; participant seated with weight on ankle extends the knee and performs knee extension, holds for 3 to 4 seconds and returns slowly to flexion on each leg.

For exercises involving weight, the weight will be determined for each participant using the ten-maximum repetition test. New tests will be held at the beginning of each phase.

#### Data analysis

The sample size was calculated using the MVIC of the muscles as the outcome and an 80% power to detect a 20% improvement, with a 5% level of significance. Based on the study by Alfredo *et al.*[28], a minimum of 17 patients were determined for each group.

Primary (MVIC of the muscles (dynamometer) and stabilometry) and secondary (pain (digital algometer), range of motion (fleximeter), and quality of life (WHOQOL-BREF and WOMAC ) outcomes will be assessed.

Descriptive statistics will be used, and data will be summarized using mean, standard deviations, and percentiles. Normality of data distribution will be tested using the Kolmogorov-Smirnov test. Normal variables and comparison among three groups of the study will be assessed at baseline and at eight weeks follow-up using Analysis of Variance. Post-hoc tests will consist of the Turkey test for parametric variables, and the Dunn’s test for non-parametric variables, and the Dunn’s test for non-parametric variables. Data processing will be performed using the SPSS™ version 13.0 (Chicago, Illinois, United States) and the level of significance will be set to 5%.

The Cohen's d method will be used to determine the effect size. The interpretation of the values will be based on the classification established by Cohen: less than 0.2 (small effect); around 0.5 (moderate effect), up from 0.8 (large effect) [29].

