#### Functional tests

The Biomec 400 v1.1™ force plate (EMG System do Brasil (EMG System do Brasil Ltda® - http://www.emgsystem.com.br - [name]. [name]) will be used for the stabilometric analysis. This system quantifies the distribution of vertical ground reaction force in a static or dynamic position with a sampling frequency of 40 Hz using four sensors (two anterior and two posterior) capable of supporting 150 Kg. Each sensor stores analog data, which are amplified, converted into digital data, recorded, and interpreted using the Biomec 400™ software program (EMG System do Brasil (EMG System do Brasil Ltda® - http://www.emgsystem.com.br - [name]. [name]). The distribution of force on the four points and changes in body sway in the anteroposterior (y axis) and mediolateral (x axis) directions will be evaluated using mean displacement and area. The force plate will be placed on a flat surface, which will be verified by levels attached to the extremities of the plate. The participants will be positioned as follows: in quiet, standing, barefoot, feet abducted at 30° and separated by 3 cm, arms alongside the body, and gaze fixed on a round target (5 cm in diameter) at the height of the glabellum positioned on a pedestal 1.5 meters from the participant. Two stabilometric readings will be performed under two different conditions (eyes open and eyes closed). Each reading will last 30 seconds, with a one-minute interval between readings.

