A portable dynamometer (Lafayette manual muscle system, model 01163, Lafayette Instrument Company, Lafayette, Indiana, United States) will be used. This device has been broadly employed in clinical practice and scientific procedures due to its good inter-examiner and intra-examiner reliability in comparison to other evaluation measures considered the gold standard for this type of evaluation [18,19]. Four five-second readings will be taken of maximum voluntary isometric contraction (MVIC) with a 30-second rest period between contractions. The participant’s hands will be crossed over the chest. Readings will be made of the quadriceps and gluteus medius, bilaterally. The first MVIC will be to familiarize the participant with the task. If a participant is unable to performed three contractions with less than 10% variability, a new set of readings will be performed. Strong, constant, verbal stimuli will be given throughout the test. The order of the MVIC readings will be randomized to avoid bias. The procedure for the gluteus medius readings will be: Participant lying on one side with the limb to be tested on top in neutral position, maintained using pillows placed between the legs. An adjustable non-elastic strap will be placed over the iliac crest and attached around the cot to stabilize the pelvis. The dynamometer will be positioned over the lateral femoral condyle under a non-elastic strap attached around the distal thigh and cot. MVIC will be solicited in the form of hip abduction [20]. The procedure for the quadriceps readings will be: Participant in the sitting position, hip flexed at 90° and knee flexed at 60°. The dynamometer will be positioned at the level of the malleoli in the anterior region under a non-elastic strap attached around the distal tibia and cot. MVIC will be solicited in the form of knee extension [21]. Strength data, measured in kilograms (Kg), will be normalized by body weight (Kg) using the following formula: Kg (muscle strength)/Kg (body mass) × 100 [18,22]. The mean of three normalized readings will be considered for the analysis.

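### The primary outcome is two measurement domains at a flat 5%, with no named variable and no rule across them, so the error rate of a positive primary claim is undefined

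*Protocol article*

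**What the plan says.** All references are to the protocol article.

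- **Data analysis, outcomes.** Two domains share primary status: "Primary (MVIC of the muscles (dynamometer) and stabilometry) and secondary (pain (digital algometer), range of motion (fleximeter". No muscle, limb, sway measure, visual condition, composite or order is attached to either.
- **Data analysis, tests.** The three groups are compared by analysis of variance at baseline and at eight weeks. Tukey or Dunn post-hoc tests follow, and "the level of significance will be set to 5" percent. No rule covers the primary variables taken together.
- **Data analysis, sample size.** The minimum of 17 per group is based on MVIC, with 80% power for a 20% improvement at 5%. The muscle, the limb and the standard deviation are not given. Stabilometry plays no part in the calculation.
- **Functional tests, dynamometry.** "Readings will be made of the quadriceps and gluteus medius, bilaterally". The only averaging described is over repeats: "The mean of three normalized readings will be considered for the analysis".
- **Functional tests, stabilometry.** "changes in body sway in the anteroposterior (y axis) and mediolateral (x axis) directions will be evaluated using mean displacement and area". Readings are taken "under two different conditions (eyes open and eyes closed".

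**The concern.** A primary outcome should fix, before the data are seen, which result decides the trial. Here two domains have that status and each can be reduced to a variable in several ways. A significant result in one limb, one muscle or one sway measure could be reported as a positive primary outcome, and nothing in the plan says whether that would be legitimate.

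Two things are at stake. The nominal 5% does not describe the error rate of a claim that can be reached by several routes. And if strength improves while balance does not, or the reverse, the plan has no rule for the conclusion.

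The post-hoc tests do not help. Tukey and Dunn deal with the three pairs of arms within a single variable and do nothing across variables.

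**Working it through.** **The plan's own figure.** The standard deviation is not given, so 17 per group cannot be reproduced, only solved backwards. Assume a two-sided comparison of two groups under the normal approximation, n = 2(1.960 + 0.842)²/d². Setting n = 17 gives d = 2.802 × √(2/17) = 0.96. Read as 20 percentage points, the improvement implies a standard deviation of about 20.8. This d is used below only to price the fix.

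**Counting the candidate variables** (from Functional tests)

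- Strength: 2 muscles × 2 limbs = 4.
- Sway: anteroposterior displacement, mediolateral displacement and area = 3 measures; × 2 visual conditions = 6.
- Total: 4 + 6 = 10.

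The count is derived; the article does not state it. Averaging over limbs would give 2 + 6 = 8. The force distribution over the four sensors is also mentioned and is left out. The smallest reading is one variable per domain, which gives 2.

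**Chance of at least one false positive, if any one significant variable counts as success**

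With k independent tests at 5%, the chance is 1 − 0.95^k:

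- k = 2: 1 − 0.9025 = 9.8%
- k = 4: 18.5%
- k = 8: 33.7%
- k = 10: 40.1%

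The variables will be correlated, and the article gives no correlations, so these are assumed. Simulating three-group analyses of variance under no effect, with 17 per group and a common correlation r, gives:

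| Variables | r = 0 | 0.3 | 0.5 | 0.7 | 0.9 |
|---|---|---|---|---|---|
| 2 | 10% | 10% | 9% | 9% | 7% |
| 4 | 18% | 18% | 16% | 13% | 10% |
| 10 | 40% | 36% | 30% | 23% | 13% |

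A common correlation across strength and sway is crude. With 0.5 to 0.9 within each domain and 0.1 between them, ten variables give about 34% down to 20%.

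**Cost of splitting the level.** At d = 0.96 and 17 per group, d/√(2/17) = 2.802.

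- Two primaries, 0.025 each: power = Φ(2.802 − 2.241) = Φ(0.560) = 71%. Keeping 80% needs 2(2.241 + 0.842)²/0.961² = 20.6, so 21 per group.
- Ten variables by Bonferroni, 0.005 each: power = Φ(2.802 − 2.807) = 50%. Keeping 80% needs 29 per group.
- One named primary at 5%: 80% at 17 per group, unchanged.

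**The case against.** The strongest reply is that the article declares two primary outcomes, not ten. The Functional tests section describes how measurements are taken and never says that each reading is a separate endpoint. A reader might infer ten declared tests and a 40% false positive rate, but the documents do not support that. The count is undetermined, and 40% needs ten independent variables. These variables include the same muscle on two limbs, displacement and area from the same recording, and the same person with eyes open and closed. This part of the objection stands, so the size has to be given as a range.

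Second, the inflation depends on an any-one-is-enough rule that the article does not state. The hypothesis in the Background lists its expected benefits jointly. If every primary variable had to be significant, the false positive rate would not exceed 5%. This stands as a condition on the figures. It does not rescue the plan, because the article adopts neither rule. Under the all-must-succeed rule, the 80% calculated for MVIC would not be the power of the trial. Nor does anything show that the authors intend to pick a variable after seeing results; the plan simply does not prevent it.

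Third, variable definitions and testing order are often left to a statistical analysis plan, and the article is a condensed text. That would answer a complaint about missing detail. Here, though, the article does state the primary outcome and the significance level, and the rule it states does not control the error of a primary claim.

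Lastly, sizing on one of two primary outcomes is common practice, and 17 is called a minimum. The lack of a calculation for stabilometry is therefore a minor matter.

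**Conclusion.** The point holds in a limited form. Two domains are primary at a flat 5%, neither is reduced to a named variable, no rule links them, and the stated post-hoc tests do not act across variables. That much rests on the text alone.

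The size is conditional. If one significant primary variable is enough, the false positive rate is about 7% to 10% with one variable per domain. If all ten derived variables are tested, it is about 13% to 40%. Both ranges cover assumed common correlations from 0.9 to 0. That is about 1.4 to 2 times the nominal level with two variables and about 2.7 to 8 times with ten. Some inflation is present at every combination examined; only its amount depends on the count and the correlation. The defect should be corrected before unblinding on the strength of the undefined primary claim, not on the 40% extreme.

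**What to change.** Before unblinding, replace the primary outcome statement by one of the following.

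1. **One primary outcome (preferred).** Name one MVIC variable at eight weeks and test it at 5%. The sponsor chooses the muscle and how the limbs are combined, to match the variable behind the sample size. The article says only that sizing used MVIC of the muscles, so it does not itself point to the quadriceps or to a limb average. Test one pre-named sway measure, in one visual condition, next and only if the first is significant. Label the remaining strength and sway variables secondary or exploratory.
2. **Two primary outcomes.** Name one MVIC variable and one sway variable and apply Holm across them, stating that either suffices for a claim about its own domain.

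In both cases, state that Tukey and Dunn cover arm pairs within a variable only.

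The change is to wording and analysis, with no new data collection. Recruitment is already under way, so it should be dated and documented as made without sight of results by group. Under option 1, some variables lose primary status. Under option 2, power at 17 per group falls to about 71% for a variable judged at 0.025, for the effect implied by that sample size, and about 21 per group would be needed to keep 80%. The loss should be stated. Bonferroni over all ten variables is a poor alternative, at about 50% power.

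### The choice between ANOVA and a rank test rests on an under-specified Kolmogorov-Smirnov pre-test; run uncorrected in groups of 17 it could cost power on a skewed sway area

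*Protocol article*

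**What the plan says.** The Data analysis section of the protocol article sets out the route in three steps.

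- The gate: "Normality of data distribution will be tested using the Kolmogorov-Smirnov test".
- The parametric route: "Normal variables and comparison among three groups of the study will be assessed at baseline and at eight weeks follow-up using Analysis of Variance".
- The comparisons after it: "Post-hoc tests will consist of the Turkey test for parametric variables, and the Dunn’s test for non-parametric variables".

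No outcome is exempt, so the rule covers the primary outcomes: "Primary (MVIC of the muscles (dynamometer) and stabilometry". Under Functional tests, sway on the force plate "will be evaluated using mean displacement and area", with eyes open and with eyes closed.

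The group size is small: "a minimum of 17 patients were determined for each group". It was set for "an 80% power to detect a 20% improvement, with a 5% level of significance", with muscle strength (MVIC) as the outcome.

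The article does not say whether the Kolmogorov-Smirnov (K-S) test carries the Lilliefors correction, whether it is applied per group, to the pooled data or to residuals, or whether any outcome may be transformed. It does not say that any outcome is skewed.

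**The concern.** Each outcome's method is chosen by a significance test on the trial's own data. Such a gate helps only if it detects departures from normality large enough to matter.

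The ordinary K-S critical value assumes that the mean and SD are known. When both are estimated from the same 17 values, the fitted curve lies closer to the data than that critical value allows for, and the test becomes very conservative. A clearly skewed outcome would then pass as normal and be analysed by ANOVA on the raw scale, where a few large values inflate the error variance.

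The primary outcome most exposed is sway area, a positive quantity that may well be right-skewed. At stake is power in a trial whose group size leaves none to spare, and a primary analysis whose form depends on how the sample happens to fall.

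**Working it through.** **1. The plan's own figure.** No SD is given, so 17 per group can only be back-solved. For two groups, two-sided 5% and 80% power, d = (1.960 + 0.842) × √(2/17) = 0.96. A 20% difference then implies an SD of 20 / 0.96 = 20.8% of the mean. The 17 can be neither confirmed nor refuted, but the implied coefficient of variation (CV) of about 21% is used in step 5.

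**2. How often the gate rejects.** Inputs: n = 17 per group and three groups (article); log-normal outcomes with log-SD 0.5 or 0.8 (assumption). The 5% critical distance at n = 17 is 0.318 for plain K-S and 0.207 with the Lilliefors correction. Simulated rejection rates:

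| Version and unit | Log-SD 0.5 | Log-SD 0.8 |
|---|---|---|
| Plain, one group of 17 (asymptotic to exact p-values) | 0.6–0.9% | 4–7% |
| Plain, at least one of three groups (asymptotic) | 2% | 13% |
| Plain, all 51 pooled (asymptotic) | 10% | 52% |
| Lilliefors, one group of 17 | 30% | 57% |
| Lilliefors, at least one of three groups | 66% | 92% |

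Under exact normality, Lilliefors flags at least one of three groups in 14% of trials, as expected: 1 − 0.95³ = 0.143.

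**3. Power, three arms of 17.** One arm is shifted by 0.93 log-SD. On the log scale the noncentrality is 17 × 0.93² × 2/3 = 9.8 on 2 and 48 degrees of freedom, which gives about 78% power. The shift is downward because the Background hypothesises better static balance, read here as less sway. It corresponds to a ratio of exp(−0.93 × 0.5) = 0.63 or exp(−0.93 × 0.8) = 0.48. The rank route is taken if any group rejects, with Kruskal-Wallis as its overall test; both are assumptions, since the article names only Dunn's test. Results from 20,000 simulated trials:

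| Analysis | Log-SD 0.5 | Log-SD 0.8 |
|---|---|---|
| Log-scale ANOVA | 78% | 78% |
| Kruskal-Wallis always | 75–76% | 75% |
| Raw-scale ANOVA always | 69% | 55% |
| Gate, plain K-S per group | 69% | 61–63% |
| Gate, plain K-S pooled | 70% | 70% |
| Gate, Lilliefors per group | 76% | 75% |

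The 61–63% range again reflects asymptotic and exact p-values. The loss under plain per-group K-S is 78 − 69 = 9 points at log-SD 0.5 and 78 − 63 to 78 − 61 = 15 to 17 points at 0.8.

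**4. Direction.** For an upward shift of the same size, the plain per-group gate gives 76% and 72–73%, so the loss is smaller, at about 2 and 5–6 points.

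**5. Muscle strength.** A CV of 20.8% corresponds to a log-SD of √ln(1 + 0.208²) = 0.21. At log-SD 0.2, raw-scale ANOVA has 76% power (downward) or 78% (upward) against 78% on the log scale, a loss of 0–2 points.

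**6. Type I error.** With no shift, every version of the two-stage rule stays between 4.4% and 5.5%.

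**The case against.** The strongest reply is that the harm depends on a detail the article leaves out. A condensed article may leave the test version and unit to an analysis plan, and with the Lilliefors correction the gate loses only about 1–3 points. This stands, and it limits the size of the point. A reader might infer that the pre-test almost never rejects at this sample size. The article does not support that as a general statement: it is true of the uncorrected test within groups, but pooling the 51 patients or applying Lilliefors changes the picture.

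Second, nothing in the article shows skewness. A reader might infer that both primary outcomes are skewed and lose power. For MVIC, the mean of three weight-normalised readings, there is no stated reason to expect strong skew, and at the implied CV the loss is negligible. Only sway area is plausibly affected, and that is an assumption. The log-scale comparator is also correct by construction for log-normal data. The fairer benchmark of Kruskal-Wallis throughout, at about 75%, still beats the plain per-group gate.

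Third, a reader might infer that the analysis is open to free choice after the data are seen. It is not: a rule is stated beforehand, the Blinding section keeps the statistician blinded until the analysis is complete, and type I error holds.

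Fourth, two further inferences fail. The article speaks of normal variables, and does not say that one outcome may take different routes at baseline and at eight weeks. Nor is it a special fault of the rank route that it ignores baseline, because the stated ANOVA is not described as baseline-adjusted either.

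What remains is that the stated rule has no good reading. Uncorrected and per group, it misses the skew it is meant to catch. Corrected, it costs little power, but at log-SD 0.5 it takes the rank route in about two trials in three and ANOVA in the third, for the same underlying outcome.

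**Conclusion.** The point holds in a limited form, as a cheap improvement. The primary analysis depends on a K-S pre-test whose version and unit are not given.

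On the least favourable reading (uncorrected, per group), and assuming a log-normal sway area with log-SD 0.5 to 0.8 and a true reduction in sway, power falls from about 78% to about 69% and 61–63% respectively. With the Lilliefors correction the loss is about 1–3 points, and what remains is a method that varies by chance, most visibly at moderate skew. MVIC loses 0–2 points. False-positive risk is not raised under any version.

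The figures rest on assumed distributions, equal groups of 17, one shifted arm and Kruskal-Wallis as the overall rank test. They show the order of magnitude and do not predict this trial's power.

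**What to change.** In Data analysis, remove the normality test as the gate between methods. For each primary outcome, name one model: ANCOVA of the eight-week value on group, adjusted for the baseline value, which is already collected.

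Fix the scale in the same place: log for sway area, and the raw scale for MVIC. Use the log for displacement only if it is recorded as a positive amplitude. The article reports sway along two axes without saying whether the value is unsigned, and the log of a signed mean is undefined.

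Check model residuals, and report a rank-based analysis as a sensitivity analysis whatever the residuals or any normality test show.

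This takes a few sentences and no new data, visits or patients. Recruitment was under way at publication, so it can be settled before outcome data are analysed. The one small cost is that log-scale results are read as ratios between groups instead of differences in area.

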Low-level laser therapy (LLLT) has properties that exert a positive influence on the proliferation of fibroblasts, collagen synthesis, and bone regeneration. LLLT also has an analgesic effect mediated by hormonal and opioid mechanisms and has therefore recently become an important tool in the treatment of OA, offering pain relief and improved knee function [9,10]. The use of phototherapy in the form of LLLT and light-emitting diode therapy, both of which operate in the red and infrared spectra, has proven effective in delaying the development of fatigue and improving muscle performance [11]. It would therefore seem advantageous to combine these two forms of phototherapy in a single device. However, clinical trials are needed to test the effects on deeper structures, such as joints, using comparable protocols and outcome measures. Due to its physiological effects, phototherapy may promote increased positive effects of preexisting treatments and may slow the degeneration process and its repercussions, such as contractures and joint deformity, which can lead to postural imbalance and the loss of muscle strength in the lower limbs, resulting in recurrent falls.

The aim of the proposed study is to analyze the effect of the incorporation of phototherapy into a therapeutic exercise program for OA of the knee. The hypothesis is that patients with OA of the knee who are treated with phototherapy combined with a therapeutic exercise program will experience a greater reduction in pain as well as improved knee range of motion, static balance, functional capacity, muscle strength, and quality of life in comparison with those treated with exercise alone.

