## Methods/Design

### Overview of research design

We propose a double-blind, placebo-controlled, randomized clinical trial to analyze the effect of the incorporation of phototherapy into a therapeutic exercise program for individuals with osteoarthritis of the knee. Participants will be recruited from clinics and hospitals and will be allocated to different groups through a randomization process using opaque envelopes containing cards stipulating one of the three following groups: 1) exercise program, 2) exercise program + phototherapy, and 3) exercise program + placebo phototherapy. Phototherapy will be performed on the knees diagnosed with OA.

The study will be divided into two evaluations and one treatment phase, to which all individuals will be submitted. Phase one is the initial evaluation phase. After recruitment, individuals who meet the eligibility criteria will undergo an initial evaluation in the following sequence: administration of the Lower Extremity Functional Scale (LEFS), the WHOQOL-BREF questionnaire and the Western Ontario and McMaster Universities Index for Osteoarthritis (WOMAC), numeric pain rating scale (NPRS) and algometry for pain, followed by a functional evaluation (stabilometry, dynamometry, range of motion (ROM), timed up-and-go test (TUGT) and the functional reach test (FRT)). Phase two is the treatment phase. Following randomization, the treatments will be performed on the knee(s) in three weekly sessions spanning eight weeks (for a total of 24 sessions). Phase 3 is the final evaluation phase. One day after the end of the treatment phase, the final evaluation will be performed, following the same sequence employed in the initial evaluation (Additional file 1).

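### The treatment comparison names no use of each participant's baseline value; naming baseline-adjusted ANCOVA would gain precision at almost no cost

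*Protocol article*

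**What the plan says.** The Data analysis section of the protocol article states that the comparison among the three groups "will be assessed at baseline and at eight weeks follow-up using Analysis of Variance". Post-hoc comparisons follow by Tukey's test (misspelled in the text) for parametric variables and Dunn's test for non-parametric ones. No covariate, change score, repeated-measures factor or group-by-time interaction is named.

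The same section sets the sample size: "an 80% power to detect a 20% improvement, with a 5% level of significance", from which "a minimum of 17 patients were determined for each group". The primary outcomes are given as "Primary (MVIC of the muscles (dynamometer) and stabilometry".

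The Overview of research design describes the same battery of measurements before treatment and again one day after treatment ends. Allocation uses "opaque envelopes containing cards stipulating one of the three following groups". No stratification or balancing on baseline strength or balance is described.

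**The concern.** Each participant supplies a baseline value of each outcome, but the only stated role for it is a between-group test at baseline. Under proper randomisation, that test examines only the play of chance, and it corrects nothing in the week-8 comparison.

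Outcomes such as muscle strength, sway, pain threshold and range of motion can be expected to vary between people and to correlate within a person over eight weeks. A comparison of week-8 values alone leaves all of the between-person variance in the error term. In the one allocation actually obtained, it also carries a fraction r of any baseline difference into the estimated effect. With a planned minimum of 17 per group, both effects can be large enough to matter.

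**Working it through.** **Inputs from the document.** Three groups; minimum 17 per group (3 × 17 = 51, a total the article does not print); 80% power; 5% significance.

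**Assumptions.** Two-sided test, equal allocation, and r (correlation of baseline with week 8) from 0.3 to 0.8. The document gives none of these.

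**The stated sample size.** It cannot be reproduced, because no SD or mean MVIC is given. Solving backwards with the normal approximation: d = (1.960 + 0.842) × √(2/17) = 2.802 × 0.343 = 0.96. If the 20% is a between-group difference, the SD would be 0.20/0.96, or about 21% of mean MVIC. So 17 is neither confirmed nor shown wrong. I use d = 0.96 as the plan's own implied effect.

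**Precision.** ANCOVA leaves residual variance SD² × (1 − r²). The comparison of change scores has variance SD² × 2(1 − r). Pairwise power comes from the noncentral t distribution with noncentrality d/√(v × 2/17), where v is the relative variance. Error df are 48 unadjusted and 47 for ANCOVA. The two-sided 5% critical value is 2.01; the Tukey value for three groups is 2.42.

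| Analysis | Relative variance v | Power, unadjusted pairwise t | Power, Tukey criterion |
|---|---|---|---|
| Week-8 only | 1.00 | 78% | 65% |
| ANCOVA, r = 0.3 | 0.91 | 82% | 70% |
| ANCOVA, r = 0.5 | 0.75 | 89% | 79% |
| ANCOVA, r = 0.7 | 0.51 | 97% | 93% |
| ANCOVA, r = 0.8 | 0.36 | over 99% | 99% |

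The first row reads 78% rather than 80% because the t distribution replaces the normal. Allowing also for estimation of the covariate slope (variance × (1 + 1/46)) lowers the ANCOVA figures by about one point or less.

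In patients, 17 per group with adjustment is worth 17/(1 − r²) without it: about 19 (r = 0.3), 23 (r = 0.5), 33 (r = 0.7) or 47 (r = 0.8).

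**If a group-by-time ANOVA was meant.** With one baseline and one follow-up, its interaction test is the comparison of change scores. Its relative variance 2(1 − r) is 1.40 at r = 0.3, 1.00 at r = 0.5, 0.60 at r = 0.7 and 0.40 at r = 0.8. It is worse than week-8 only when r is below 0.5. It never beats ANCOVA apart from one degree of freedom, because 2(1 − r) − (1 − r²) = (1 − r)² ≥ 0.

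**Chance imbalance.** The standard error of a baseline difference between two arms is √(2/17) = 0.343 SD. The probability that it exceeds 0.5 SD in either direction is 2 × [1 − Φ(0.5/0.343)] = 2 × [1 − Φ(1.458)] = 14% for one pair. By simulation it is about 31% for the largest of the three pairs.

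A fraction r of the imbalance enters the week-8 comparison: at r = 0.7, 0.7 × 0.5 = 0.35 SD. Given such an imbalance against the active arm, the conditional standard error is √(0.51) × 0.343 = 0.245 and the critical difference is 1.960 × 0.343 = 0.672. Conditional power for d = 0.96 is then 1 − Φ((0.672 − (0.961 − 0.35))/0.245) = 1 − Φ(0.25), about 40%.

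**The case against.** **The planned analysis is valid.** This stands. Comparing week-8 values between randomised groups is unbiased over repeated randomisations and keeps its type I error. Chance imbalance is already part of its standard error, so lost precision and exposure to imbalance are largely two views of the same variance. The 0.35 SD shift and the 40% power are conditional on an uncommon allocation. A reader might infer that the results would be biased or the test invalid; the document does not support that.

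**The improvement wording is no contradiction.** The sample size refers to "80% power to detect a 20% improvement", and the Background hypothesis says that phototherapy patients "will experience a greater reduction in pain as well as improved knee range of motion". A reader might infer that testing week-8 levels answers a different question. It does not: under randomisation, the expected group difference at week 8 equals the expected group difference in change.

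**The sentence is loose.** A repeated-measures ANOVA might have been intended. The text does not say so, and two separate ANOVAs cannot be asserted as certain either. This limits how firmly the plan can be said to ignore baseline. The recommendation is unaffected, since ANCOVA is the better choice under both readings.

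**The size depends on r.** This also stands. No correlation is given for any outcome, and a single range is applied to all of them. At r = 0.3 the gain is only about 4 to 5 points of power.

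**Non-normal outcomes.** Dunn's test as described makes no use of baseline, so that branch does not answer the point. A fix must cover it, as well as Tukey's control of multiplicity.

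**Conclusion.** This is a worthwhile improvement at almost no cost, not a validity error. As written, the plan names no use of the baseline value in the treatment comparison. At the plan's implied effect, the gain from adjustment in two-sided pairwise power is about 4 points at r = 0.3, 11 at r = 0.5 and 19 at r = 0.7. Under the Tukey criterion the corresponding gains are about 5, 14 and 28 points.

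These figures rest on the assumed r, on 17 analysed per group, and on reading the 80% power as a two-sided pairwise comparison. The direction of the gain depends on none of these, unless r is close to zero. The adequacy of 17 per group is not in question here, because the document does not give the figures needed to test it.

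**What to change.** For each continuous outcome, replace the ANOVA sentence with an ANCOVA: week-8 value as response, group as factor, and the baseline value of the same outcome as covariate. In addition:

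- Report adjusted pairwise differences with 95% confidence intervals, keeping multiplicity control across the three pairwise comparisons.
- For clearly non-normal outcomes, use a transformed or rank-based ANCOVA, so that this branch also uses baseline.
- Present baseline values descriptively and drop the significance test at baseline.

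The cost is a few sentences and one degree of freedom per model, with no new data or patients. The Trial status section says recruitment is under way, so the change should be recorded before the allocation is revealed to the statistician.
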